### Sample size calculation

The incidence rate of PPCs is 39% in the low PEEP group [15]. The two-tailed chi-squared test is performed, and we estimate that 188 patients are required to provide 90% power to detect a 50% relative difference between the two groups (39% to 20%), and type I error probability was 0.05. Given that the follow-up lost rate is 10%, 208 cases in total are needed. Analysis is computed by using G-Power (version 3.1; Informer Technologies, Inc. Universität Kiel, Germany).

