It should be noted that these studies included only open surgeries or various types of abdominal surgery; they did not include patients planning to undergo robot-assisted laparoscopic surgery. Furthermore, it is necessary to consider the effects of steep Trendelenburg (sT) positioning and pneumoperitoneum (PnP) on airway pressure and pulmonary function [18], which can increase intra-abdominal pressure and enhance the cranial displacement of the diaphragm. This displacement will decrease lung compliance and lung volumes and increase lung resistance. Adopting a PEEP of 7 cm H_2_O during RALP, which could improve arterial oxygenation without causing excessive peak airway pressure, has been recommended [19]. Also, a lung-protective ventilation strategy with a lower tidal volume (V_t_) of 6 mL/kg and a PEEP of 8 cm H_2_O was associated with less impaired postoperative pulmonary functions in patients undergoing RALP in another recent study [20].

The role of PEEP during the intraoperative period in preventing PPCs for robot-assisted laparoscopic surgery has not been clearly defined. This study may further improve our knowledge regarding the effects of intraoperative PEEP on PPCs, survival rates, and in-hospital stays in patients undergoing robot-assisted laparoscopic radical resection for bladder cancer or prostate cancer.

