### Statistics

Normally distributed variables will be expressed as the mean ± standard deviation and will be compared with the Student’s *t* test. Categorical variables will be compared by using the chi-squared test or Fisher’s exact test. Non-normal continuous variables will be expressed as median (interquartile range) and evaluated with the Mann–Whitney *U* test. Intention-to-treat analyses are performed to compare the composite outcome measure at 7 days in the two groups by the chi-squared test (or Fisher’s exact test as appropriate), and multiple logistic regression analysis adjusting will be performed to identify various risk factors (for the primary outcome and the pulmonary complications at POD 30). Adjusted analyses are performed with the use of robust Poisson generalized-linear-model regression for continuous outcomes and are presented as relative risks with 95% confidence intervals. A *P* value of less than 0.05 will be considered statistically significant, and all reported *P* values will be two-sided. Interim analysis of safety will be conducted after enrollment of the first 200 patients. All analyses will be conducted by using SPSS version 18.0 (SPSS, Chicago, IL, USA) software.

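### The 188 evaluable patients give about 82% power for 39% versus 20%, not the stated 90%

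*Protocol article*

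**What the plan says.** All the inputs are given in the protocol article.

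- Control rate (Sample size calculation): "The incidence rate of PPCs is 39% in the low PEEP group", taken from the trial cited as reference 15.
- Effect (same section): the aim is "to detect a 50% relative difference between the two groups (39% to 20"%).
- Test and error rate (same section): "The two-tailed chi-squared test is performed" and "type I error probability was 0.05". The Statistics section agrees on sidedness: "all reported *P* values will be two-sided", with a 0.05 threshold.
- Claimed result (Sample size calculation): 188 patients for 90% power, in the words "we estimate that 188 patients are required to provide 90% power to detect a 50% relative difference between the two groups (39% to 20"%).
- Inflation (same section): "Given that the follow-up lost rate is 10%, 208 cases in total are needed". The Abstract also gives 208 as the total.
- Allocation (the section on blinding, data collection, randomization and record-keeping): 1:1.

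Because 208 is a total and is 188 inflated for loss, 188 is also a total, that is 94 per arm.

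**The concern.** The test, alpha, two rates, power and sample size are stated together and can be checked against one another. A difference of 39% versus 20% at 90% power and two-sided 0.05 needs clearly more than 94 per arm.

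Power is the protocol's assurance about the primary endpoint. If the trial finds no significant difference, readers will take the result as having had a 10% chance of missing a halving of risk. If the real chance is nearly twice that, a negative finding carries less weight than the protocol claims. The Discussion says the findings might change ventilation practice, so this matters for how a null result is used.

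**Working it through.** **Inputs.** p1 = 0.39, p2 = 0.20, two-sided alpha 0.05 (z = 1.960), power 90% (z = 1.2816), 1:1 allocation, 94 per arm evaluable. All come from the protocol article as listed above.

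**Attempt to reproduce 188.** The pooled-variance formula for two proportions is

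n per arm = [z_alpha × √(2p̄(1−p̄)) + z_beta × √(p1(1−p1) + p2(1−p2))]² / (p1−p2)²

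with p̄ = (0.39 + 0.20)/2 = 0.295.

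- √(2 × 0.295 × 0.705) = 0.6449
- √(0.39 × 0.61 + 0.20 × 0.80) = 0.6308
- n = (1.960 × 0.6449 + 1.2816 × 0.6308)² / 0.19² = (1.2641 + 0.8084)² / 0.0361 = 118.98, so 119 per arm
- Evaluable total: 2 × 119 = 238. After 10% loss: 238 / 0.9 = 264.4, so 265.

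The stated 188 is not reproduced. The shortfall is 238 − 188 = 50 evaluable patients (21%). The step from 188 to 208 is consistent to within one patient (188 / 0.9 = 208.9), so the problem lies in the 188 itself.

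**Power at the stated size.**

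z_beta = [(p1−p2)√n − z_alpha × 0.6449] / 0.6308 = (0.19 × √94 − 1.2641) / 0.6308 = (1.8421 − 1.2641) / 0.6308 = 0.916

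This gives 82.0% power and a type II error of 18.0%, which is 1.8 times the stated 10%.

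**Other two-sided readings.**

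| Reading | Power at 94 per arm | Power at 104 per arm (no loss) | Evaluable N for 90% |
|---|---|---|---|
| 39% vs 20%, pooled formula | 82.0% | 85.7% | 238 |
| 39% vs 20%, noncentral chi-squared | 81.5% | 85.2% | about 242 |
| 39% vs 20%, exact enumeration, Pearson test | 82.2% | 86.2% | not computed |
| 39% vs 19.5% (exact halving), pooled | 84.2% | 87.7% | 226 |
| 39% vs 19% (more generous than the text), pooled | 86.2% | 89.4% | 214 |

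For 39% vs 20%, the unpooled and arcsine methods need 232 and 238. A continuity-corrected calculation needs 260. With 94 per arm, the pooled formula reaches 90% power only if the rate falls to about 17.9%.

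**Possible source (inference only).** One-sided 0.05 calculations come close to 188 at 90% power: 97 per arm (194) for 20% and 92 per arm (184) for 19.5% with the pooled formula, and 190 in total for 20% with the unpooled formula. One-sided power at 94 per arm is 89.2% for 20%. The article does not show the software settings, so this cannot be confirmed, and it would contradict the two-tailed wording.

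**Dependence on the control rate.** The 39% comes from a trial that the Background describes as open abdominal surgery. The Background adds that "these studies included only open surgeries or various types of abdominal surgery" and did not include patients planned for robot-assisted surgery. If PEEP exactly halves the risk, pooled two-sided power at 94 per arm is about 48% at a 20% control rate, 70% at 30%, 84% at 39% and 95% at 50%. The rates other than 39% are assumptions for illustration.

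**The case against.** The strongest reply concerns weight, not arithmetic. The error biases no estimate and leaves the type I error unchanged. Power of 82% to 84% is above the commonly accepted 80%, so the trial remains viable at its planned size. That is correct, and it is why a larger sample is not required.

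A second point is that 82% is the less favourable reading. An exact halving to 19.5% gives a type II error of 15.8%, about 1.6 times the stated 10%. With intention-to-treat analysis, planned replacement of missing values and a 7-day endpoint, the number analysed could lie between 188 and 208, where power rises to at most 87.7% under a halving. This is fair, and the range should be shown. But the text ties the 90% to 188 patients and to 20%, and neither relaxation reaches 90%.

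Third, with Fisher's exact test or a continuity correction, power at 94 per arm would be about 78%. That figure should carry little weight: the planned test is chi-squared, and about 94 × 0.295 ≈ 28 events per arm are expected, so small counts would not trigger Fisher's test.

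Fourth, whether 39% transfers to this population is a planning judgement. The Background gives a range of 12% to 58% for abdominal surgery, and the Discussion treats steep Trendelenburg positioning with pneumoperitoneum as a risk factor, so a higher rate is also possible. This stands. The control-rate figures are context and the finding does not depend on them.

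**Conclusion.** The stated power is wrong as written. With 94 evaluable patients per arm, two-sided alpha 0.05 and 39% versus 20%, power is about 82%. The type II error is about 18%, nearly double the 10% claimed. Power of 90% needs 238 evaluable patients.

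This rests only on the protocol's own inputs, with 188 read as a total. Reading it as per arm would conflict with the total of 208 and would give 98% power. The conclusion does not depend on the approximation used or on the rounding of the 50% reduction.

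The consequence is a misdescribed design property, not an invalid trial. It must be corrected because it governs how a null primary result is read.

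**What to change.** Restate the sample size paragraph so that its figures agree. Suggested wording: 188 evaluable patients (208 randomised) give about 82% power, at a two-sided alpha of 0.05 with a chi-squared test, to detect a difference between 39% and 20%; 90% power applies only to a fall to about 18%. State the software procedure and inputs, including sidedness, so that the figure can be reproduced. Do not describe the trial as having 90% power in later reports.

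It would also help to show power for control rates on both sides of 39%, because that rate comes from a different surgical population. This is advisable but not essential to the correction.

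Restating the power is a wording amendment. It needs no more patients; its only cost is a less favourable stated power. If 90% is considered essential, the alternative is 238 evaluable patients, about 265 randomised (266 for equal arms), which is 57 or 58 more than the planned 208.

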### Adverse events and interruption of the trial

All patients will be continuously monitored during the study, including daily visits during in-hospital and daily phone-call visits during the out-of-hospital follow-up period (until POD 30). All serious adverse, unexpected, or possibly related events will be recorded in the CRF and will be reported to the data monitoring and safety committee (DMSC). DMSC can recommend that the study should be stopped unless there is evidence that patient is safety (a between-group difference in serious adverse events or in 30-day mortality is found).

## Discussion

In this pragmatic, prospective, randomized controlled trial of patients undergoing robot-assisted laparoscopic radical resection for bladder cancer or prostate cancer, our aim will be to assess not only possible single effects of PEEP levels on major PPCs from those of lower tidal volumes and RM but also relevant clinical parameters associated with alterations in pulmonary function, such as chest x-ray, abnormalities, mCPIS, arterial oxygenation/peripheral oxygen saturation in air, and changes in dyspnea/cough/secretions. Our findings might change the current practice of mechanical ventilation in patients undergoing robot-assisted laparoscopic radical resection for bladder cancer or prostate cancer.

Notably, mechanical ventilation itself is one of the major contributors to PPCs [29]. sT positioning together with pneumoperitoneum is also an important risk factor for PPCs [30]. Intra-abdominal pressure is frequently higher than airway pressure during PnP with carbon dioxide (CO_2_) for laparoscopic surgery. This pressure gradient usually causes cephalad displacement of the diaphragm and collapses adjacent pulmonary tissues. PnP also decreases respiratory compliance and arterial oxygenation [31]. All of these influences on PnP lead finally to atelectasis [32]. The major difference between robot-assisted surgeries and other laparoscopic surgeries is the sT positioning, which will further decrease respiratory compliance and vital capacity.

On the other hand, PEEP is thought to prevent the development of atelectasis by keeping the airways open and maintaining adequate gas exchange at the end of the expiratory period during PnP [9]. Certainly, the level of PEEP should be adopted according to the patient’s and surgical characteristics as well as to the patient’s positioning.

The optimal PEEP has not yet been defined in patients undergoing robot-assisted laparoscopic surgery, even though adopting a PEEP of over 5 cm H_2_O in patients undergoing laparoscopic surgery is recommended [11]. One study recommended adopting a PEEP of 7 cm H_2_O during RALP [19], and another recent study found that a PEEP of 8 cm H_2_O was the optimal level of PEEP in patients undergoing RALP [20]. As we know that low levels of PEEP are potentially associated with atelectasis by promoting repeated opening and closing of small airways [33]. However, higher levels of PEEP may increase mean airway pressure of the respiratory system and likely even impair hemodynamics.

There is an increasing number of highly qualitative randomized controlled trials regarding intraoperative mechanical ventilation and PPCs in both abdominal surgeries [10, 11] and laparoscopic surgeries [32], whereas direct assessment of the effect in patients undergoing robot-assisted laparoscopic radical resection for bladder cancer or prostate cancer is still lacking. The potential significance of this trial is that it may provide evidence of the effects of intraoperative PEEP on PPCs in patients undergoing robot-assisted laparoscopic radical resection for bladder cancer or prostate cancer.

There are some potential strengths of the present trial protocol. First, the included patients will undergo elective robot-assisted laparoscopic radical resection for bladder cancer or prostate cancer with longer anesthesia duration, which is a potential risk factor for PPCs [7]. Second, this trial design includes instructions for fluid management standardization and analgesic treatments during the perioperative period. Third, the adopting ARISCAT score is considered the most valuable tool for predicting PPCs, although various scores have been developed for predicting PPC incidence based on various countries and surgical populations [9].

## Trial status

The study protocol version number is V1.0 (September 10, 2018). It is first submitted to the ethics committee of Zhejiang Provincial People’s Hospital (People’s Hospital of Hangzhou Medicine College) on September 10, 2018, and finally approved on October 22, 2018 (Additional files 6 and 7). The first participant is expected to be recruited before March 2019, and the estimated completion date of recruitment is October 2021.

## Abbreviations

ARISCAT: Assess Respiratory Risk in Surgical Patients in Catalonia
ASA: American Society of Anesthesiologists
BIS: Bispectral index
BMI: Body mass index
CONSORT: Consolidated Standards of Reporting Trials
CRF: Case report form
CT: Computer tomography
DMSC: Data monitoring and safety committee
ECG: Electrocardiogram
EtCO_2_: End-tidal carbon dioxide tension
FiO_2_: Fraction of inspired oxygen
IBW: Ideal body weight
ICU: Intensive care unit
mCPIS: Modified clinical pulmonary infection score
PACU: Post-anesthesia care unit
PEEP: Positive end-expiratory pressure
PnP: Pneumoperitoneum
POD: Postoperative day
PPC: Postoperative pulmonary complication
RALP: Robot-assisted laparoscopic radical prostatectomy
RM: Recruitment maneuver
SpO_2_: Oxygen saturation
sT: Steep Trendelenburg
V_T_: Tidal volume
